### Planned statistical analyses

As recommended by the Consolidated Standards of Reporting Trials statement for non-inferiority trials,^69^ we will perform both intention-to-treat (ITT) and per-protocol (PP) analyses. For the primary outcome, ITT and PP analyses should reach the same conclusion to consider results to be robust. For the remaining outcomes, the ITT analysis will be the primary analysis, the PP analysis a secondary analysis.

In the ITT analysis, all randomised patients will be analysed within the treatment group to which they were randomised. In the PP analysis, patients with protocol violations will be excluded (crossover to study treatment from other group; patients receiving a different type or dose of anticoagulation than requested by the study protocol; patients with missing primary outcome data; patients violating relevant eligibility criteria; patients stopping study treatment within 1 month after randomisation, or patients in whom the diagnosis of isolated SSPE was refuted by the central CTPA review panel).

We will describe the prevalence of recurrent VTE, clinically significant bleeding (including its individual components, major and clinically relevant non-major bleeding), and all-cause mortality at 90 days after randomisation with 95% Wilson CIs by treatment group. Non-inferiority of the primary outcome (VTE recurrence) among patients in the clinical surveillance versus the anticoagulation group will be assessed based on the Agresti-Caffo CI for risk difference.^68^ If the upper limit of the one-sided 95% Agresti-Caffo CI will be lower than the prespecified non-inferiority margin, clinical surveillance will be considered non-inferior to anticoagulation. For secondary outcomes, we will calculate the risk difference with a two-sided 95% Agresti-Caffo CI and compare groups using an exact binomial test.^68^

PEmb-QoL dimension scores at 30 and 90 days as well as the change in scores from baseline will be presented by treatment group as means with 95% CIs. The change in dimension scores and the differences in the change between groups will be analysed using a repeated-measures, linear mixed-effects model adjusted for the respective baseline value. Functional status, which is measured on a scale from 0 (no functional limitations) to 5 (death) at 90 days, will be presented as median and IQR and compared between groups using the non-parametric Wilcoxon rank-sum test. Count data (subsequent hospitalisations, outpatient visits) will be presented by treatment group as rate with an exact 95% Poisson CI and compared using a rate ratio and exact p value. Time-to-event outcomes (initial LOS, time to return to work/usual activities) will be presented as medians and IQRs. For LOS, we will compare groups using the Wilcoxon rank-sum test. For return to work, we will display Kaplan-Meier curves and compare groups by the log-rank test. An alpha level of <0.05 will define statistical significance.

In secondary analyses, we will calculate the cumulative incidence and the difference in cumulative incidence of VTE recurrence and clinically significant bleeding, correcting for withdrawals and losses to follow-up by censoring and for death unrelated to VTE recurrence or bleeding as a competing event. All-cause mortality will be assessed likewise, however, a competing event does not apply. In a further secondary analysis, we will use model-based approaches for all outcomes. For time-to-event outcomes (VTE recurrence, clinically significant bleeding, LOS, return to work/usual activity), we will use competing risk regression according to Fine and Gray,^70^ accounting for non-VTE/non-bleeding-related death or all-cause death as a competing event. For mortality, we will use Cox regression. For count data, we will use a negative binomial model, and also consider zero-inflation. In case of heterogeneity across sites, we will adjust models for site using random-effects models.

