### Criteria for discontinuation of the study medication and unblinding

In participants requiring prophylactic or therapeutic anticoagulation during the study period for reasons other than the index SSPE or if treatment with another prohibited agent is necessary (ie, strong CYP3A4 inhibitors or inducers, dual antiplatelet therapy, GP IIb/IIIa inhibitors), the study drug should be temporarily interrupted and restarted as soon as possible following discontinuation of the prohibited medication. Patients who develop any condition requiring permanent therapeutic anticoagulation (eg, atrial fibrillation) should permanently discontinue the study drug. If an invasive procedure or surgical intervention is required, the study medication should be stopped at least 24 hours prior to an elective intervention, or immediately for emergency procedures. If objectively confirmed recurrent VTE or pregnancy is diagnosed during the treatment period, the study drug should be discontinued and treatment allocation unblinded. Similarly, in case of major bleeding, the study drug should be stopped and unblinding may be necessary if emergency anticoagulation reversal is indicated.

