### Primary and secondary outcomes

The primary (efficacy) outcome is the proportion of recurrent, clinically symptomatic, objectively confirmed VTE within 90 days of randomisation, defined as recurrent PE or lower limb DVT.^50 51^ The objective diagnostic criterion for PE, based on available radiographic reports, is a new intraluminal filling defect on CTPA or pulmonary angiography; a perfusion defect involving at least 75% of a segment, with corresponding normal ventilation (ie, high probability lung scan); the confirmation of new PE at autopsy; or objectively confirmed proximal DVT of the lower extremity in patients with symptoms of PE. The objective diagnosis of DVT is the non-compressibility of a venous segment on CUS or an intraluminal filling defect on contrast venography. Because compression of iliac veins and the inferior vena cava may be technically difficult, additional diagnostic criteria for iliac and caval DVT also include abnormal duplex flow patterns compatible with thrombosis or an intraluminal filling defect on CT or MRI venography.^52^ Both proximal and distal DVTs are considered.

Separate secondary (safety) outcomes include the proportion of clinically significant bleeding and all-cause mortality 90 days following randomisation. Clinically significant bleeding is a composite endpoint of major and clinically relevant non-major bleeding. Major bleeding is defined as fatal bleeding, symptomatic bleeding at critical sites (intracranial, intraspinal, intraocular, retroperitoneal, intra-articular, pericardial or intramuscular with compartment syndrome), or bleeding with a reduction of haemoglobin ≥20 g/L, or bleeding leading to transfusion of ≥2 units of packed red blood cells according to the definition of the International Society on Thrombosis and Haemostasis.^53^ Clinically relevant non-major bleeding is defined as overt bleeding that does not meet criteria for major bleeding but is associated with a medical intervention, unscheduled physician contact (visit or telephone call), temporary cessation of the study drug, pain or impairment of activities of daily life.^54^

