### Sample size calculation

Assumptions on VTE recurrence risk are based on data from 127 low-risk patients with isolated SSPE who received anticoagulants (warfarin or low-molecular-weight heparin), showing a VTE recurrence risk of 0.8% at 90 days after diagnosis.^23^ We chose an absolute non-inferiority margin of 3.5% on the basis of recruitment feasibility, clinical acceptability and previous studies. This corresponds to a difference which is considered acceptable by most physicians and patients for the following reasons. First, our margin is within the range of the 3-month VTE recurrence proportion (0.5%–5%) below which thrombosis specialists would not initiate anticoagulation for PE.^61^ Second, the definition of a clinically acceptable non-inferiority margin for recurrent VTE must also take into account the potential benefits of withholding anticoagulation, that is, the substantially lower risk of clinically significant bleeding (<1% vs 7% within 3 months for patients receiving anticoagulants).^5 23 25 62^ Indeed, a patient group with PE who was involved in the trial planning process indicated that given the bleeding risk associated with anticoagulants, a VTE recurrence proportion of <5% seemed acceptable. Finally, similar non-inferiority margins (3%–5%) have been used in key studies comparing different drug treatment regimens and inpatient versus outpatient management for acute VTE.^42 44 63–67^

To determine the sample size, we used a Monte-Carlo simulation approach based on an Agresti-Caffo CI for risk difference.^68^ Assuming a baseline VTE recurrence proportion of 1.0% at 90 days in both treatment groups, an absolute margin of 3.5% defining non-inferiority for clinical surveillance and a sampling ratio of 1:1 allowing 5% attrition (dropouts, including patients who died from non-VTE-related causes) in each group during 90 days, we estimated that 276 patients (138 per group) would result in at least 80% power to establish non-inferiority at an one-sided type I error of 5%.

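### Read literally, the per-protocol rule on early stopping removes first-month primary events, which weakens per-protocol as the robustness check on non-inferiority

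*Protocol article*

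**What the plan says.** Four statements in the protocol article bear on this.

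- **Primary and secondary outcomes.** The primary outcome is "the proportion of recurrent, clinically symptomatic, objectively confirmed VTE within 90 days of randomisation".
- **Criteria for discontinuation of the study medication and unblinding.** "If objectively confirmed recurrent VTE or pregnancy is diagnosed during the treatment period, the study drug should be discontinued and treatment allocation unblinded". The same section adds that "in case of major bleeding, the study drug should be stopped". Under Control, treatment runs through the 90-day study period, so every first-month recurrence falls within it.
- **Planned statistical analyses, PP set.** Patients with protocol violations are excluded, and a bracketed list says which. One item is "patients stopping study treatment within 1 month after randomisation". Another is "patients receiving a different type or dose of anticoagulation than requested by the study protocol". Neither is limited by reason or by timing relative to an outcome event.
- **Planned statistical analyses, role of PP.** "For the primary outcome, ITT and PP analyses should reach the same conclusion to consider results to be robust". For all other outcomes, ITT is primary and PP secondary.

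**The concern.** Membership of the PP set depends on the outcome that the set is used to measure. A patient with a confirmed recurrence on day 12 stops study drug because the protocol says so, has then stopped within a month, and so meets a listed exclusion. The event and the patient both disappear from PP.

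The loss is not neutral between arms. Placebo is the experimental arm. If surveillance is worse, more recurrences occur there and more are deleted there, so the PP difference shrinks in exactly the situation that a PP analysis in a non-inferiority trial is meant to expose. With about 1% of patients expected to have an event, the test turns on one or two events. Early major bleeds drop out of the PP bleeding analysis by the same route, though that analysis is only secondary.

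**Working it through.** **Inputs from the article (Sample size calculation; Planned statistical analyses).** 138 per group; 5% attrition; recurrence 1.0% in both groups; margin 3.5 percentage points; non-inferiority if the upper limit of the one-sided 95% Agresti-Caffo interval is below the margin.

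**Assumed.** The share q of recurrences in month 1 is not in the article; 30%, 50% and 67% are shown. Every such patient is taken to stop drug as directed, and no other exclusion is applied.

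**Formula.** With x1 of n1 events under surveillance and x2 of n2 under anticoagulation, p1 = (x1+1)/(n1+2) and p2 = (x2+1)/(n2+2). The upper limit is

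U = p1 − p2 + 1.645 × √[p1(1−p1)/(n1+2) + p2(1−p2)/(n2+2)].

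**Step 1: the plan's own figure.** 138 × 0.95 = 131.1, so 131 evaluable per arm. Exact binomial enumeration at 1.0% v 1.0% gives 80.8% power, which reproduces the stated figure of at least 80%.

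**Step 2: how few events decide the test.** Take 2 v 0 events, 131 per arm.

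- ITT: p1 = 3/133 = 0.02256, p2 = 1/133 = 0.00752, standard error 0.01490. U = 0.01504 + 1.645 × 0.01490 = 3.95%, a fail.
- PP with one early surveillance event deleted (1/130 v 0/131): p1 = 2/132 = 0.01515, standard error 0.01301. U = 0.00763 + 1.645 × 0.01301 = 2.90%, a pass.

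With 3 v 1 events, deleting two early surveillance events moves U from 4.49% (fail) to 2.50% (pass). Deleting only one leaves 3.52%, still a fail.

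**Step 3: bias in the PP difference.** If a share q of events leaves with its patients, the PP rate becomes p(1−q)/(1−pq). At 4.5% v 1.0% and q = 0.5 this is 0.0225/0.9775 = 2.30% v 0.005/0.995 = 0.50%. A true difference of 3.5 points appears as 1.80 points.

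**Step 4: pass probabilities with the true difference at the margin (4.5% v 1.0%, 131 per arm).** The ITT test passes 6.5% of the time.

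| q | PP passes | ITT and PP both pass | PP passes, ITT fails |
|---|---|---|---|
| 0 | 6.5% | 6.5% | 0% |
| 0.30 | 13% | 5.8% | 7% |
| 0.50 | 24% | 5.8% | 18% |
| 0.67 | 44% | 6.0% | 38% |

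The last column is the second minus the third.

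**Step 5: the same at the planned rates (1.0% v 1.0%).** With q = 0.5, PP passes 89.6% of the time and both pass about 79%, so PP passes while ITT fails in about 11% of trials. The chance that both pass falls only from 80.8% to about 79%.

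**The case against.** **ITT protects the conclusion.** A reader might infer from the PP column that the trial's chance of a false non-inferiority claim rises to 24% or 44%. It does not. ITT keeps every randomised patient and every event, and the two analyses must agree. The joint pass probability stays between 5.8% and 6.5% and never exceeds that of ITT alone. This part of the objection stands in full and limits the point to the value of PP as a check.

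**The list is headed protocol violations.** A patient whose drug is stopped as the protocol directs has not violated it, so an ordinary reading might keep that patient in. This is fair, and it means that deletion is the literal reading rather than a certainty. But the list is what defines a violation here, and it names early stopping without exception. Leaving the choice until the events are known would make it data-dependent, on a handful of events.

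**Recurrences after month 1.** The crossover and other-anticoagulant exclusions have no time limit, so a reader might infer that any treated recurrence is excluded and that PP would contain no events at all. The text does not support this. Treating a recurrence after directed discontinuation is not clearly a departure from what the protocol requests, nor clearly a crossover to the other group's study treatment. A pre-event limit on these items is worth adding for clarity only.

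**It belongs in the SAP.** Derivation detail often does, and a separate plan may settle it. The exclusion itself, however, is stated in the article, and as stated it conflicts with the purpose of the analysis.

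**Conclusion.** The point holds in a limited form and should be fixed. Two sections of the article, followed literally, take first-month primary events out of an analysis on which the robustness of the primary result depends. The direction of the bias, towards non-inferiority when surveillance is worse, does not depend on any assumption about timing.

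The size does. It rests on the assumed share q, 131 evaluable patients per arm and no other exclusions. If 30% to 67% of recurrences are early, a PP test that should pass 6.5% of the time at the margin passes 13% to 44% of the time. If half are early, PP passes while ITT fails in about 18% of trials at 4.5% v 1.0%, and in about 11% when the arms are truly equal at 1.0%. Under the plan's rule such a trial's primary result would not count as robust, because of how the set was defined. The chance of a false robust claim is not raised. The bleeding consequence is minor, since PP is secondary there.

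**What to change.** Amend the PP definition in the protocol or SAP to say that:

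1. PP exclusions count only deviations that occur before the patient's first adjudicated outcome event.
2. Patients whose study drug was stopped because of an adjudicated recurrent VTE, clinically significant bleeding or death stay in the PP set and are counted.
3. For clarity, the same pre-event limit applies to the crossover and other-anticoagulant exclusions.

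This changes the analysis set only; the rules for stopping study drug are untouched. The cost is about one sentence of text and a comparison of the deviation date with the event date when the set is derived. The article already plans to record the dates of outcome events and interruptions of study drug, so no extra data are needed. It should be settled before unblinding.

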### Ancillary outcomes

Ancillary outcomes include health-related quality of life and functional status, both important patient-centred outcomes and medical resource utilisation, an economically relevant efficiency measure. Disease-specific, health-related quality of life at baseline, 30 and 90 days after the index PE is assessed using the Pulmonary Embolism Quality of Life (PEmb-QoL) questionnaire.^56 57^ The PEmb-QoL is a validated, self-administered 40-item questionnaire to quantify quality of life in patients having experienced PE. Functional status is measured at 90 days after randomisation using the post-VTE functional status scale.^58 59^ This scale has been proposed to assess functional limitations after VTE, covering aspects of daily life (including limitations in usual activity and changes in lifestyle) that are affected by the consequences of VTE and its complications. The assessment is done using a short, structured interview 90 days after randomisation.

The following measures of medical resource utilisation and productivity are assessed^44 60^: initial length of stay (LOS), subsequent overall hospitalisations as well as overall ED and physician outpatient visits within 90 days of randomisation, and time to return to work in workers or usual activities (eg, household) in non-workers. Information on these outcomes are obtained from the participant during the follow-up interviews, by interview of the patient’s primary care physician and by hospital chart review. Subsequent healthcare contacts are classified as potentially related to VTE if a patient had chest or leg symptoms or signs (dyspnoea, chest pain, pleural effusion or leg pain or swelling), or bleeding complications.

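### For outpatient visits, the first-line exact Poisson interval and p value ignore clustering within patients; the negative binomial model already planned should be the main comparison

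*Protocol article*

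**What the plan says.** The Ancillary outcomes section of the protocol article ranks medical resource utilisation among the ancillary outcomes: "Ancillary outcomes include health-related quality of life and functional status, both important patient-centred outcomes and medical resource utilisation". The counts it collects are "subsequent overall hospitalisations as well as overall ED and physician outpatient visits within 90 days of randomisation". They are all-cause, and one patient can contribute several.

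The Planned statistical analyses section then gives two analyses of these counts.

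- First line: "Count data (subsequent hospitalisations, outpatient visits) will be presented by treatment group as rate with an exact 95% Poisson CI", with the arms "compared using a rate ratio and exact p value". The threshold is "An alpha level of <0.05 will define statistical significance".
- Later, at a lower rank: "In a further secondary analysis, we will use model-based approaches for all outcomes". Within that set: "For count data, we will use a negative binomial model, and also consider zero-inflation".

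The section mentions no robust or scaled variance for the first-line comparison. It does not say which result prevails if the two analyses disagree.

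**The concern.** An exact Poisson interval and an exact Poisson rate-ratio test treat every visit as an independent event at a common rate, so the variance of the per-patient count is taken to equal its mean. Outpatient visits seldom behave like that. Some patients attend often and many not at all, and one episode can lead to several linked contacts. By naming a negative binomial model and possible zero-inflation, the plan itself allows for this, yet the interval and p value that come first rest on the assumption that the model relaxes.

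The stake is a claim about resource use. The Objectives and hypotheses section states that surveillance is expected to reduce it, and the Conclusion section names lower resource use as a possible benefit. If the variance is understated, a chance imbalance caused by a few frequent attenders can be called significant, in either direction.

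**Working it through.** **Inputs from the protocol article.** The arm size comes from the Sample size calculation section: "276 patients (138 per group) would result in at least 80% power". The significance level is 0.05; its sidedness is not stated, and two-sided is assumed.

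**Inputs that are assumed.** The article gives no mean, variance or dispersion for any count. The 90-day means per patient are taken as 0.1 to 0.2 hospitalisations, 0.3 ED visits and 2 to 4 outpatient visits. Counts are negative binomial with variance μ + kμ², and k runs from 0 (Poisson) to 2. The article does not name the exact test. It is read here as the conditional Poisson test, which compares one arm's total with a binomial(0.5) distribution given the overall total.

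**The plan's own figure.** There is none for the count outcomes. The arm size was reproduced only as a check. With 1.0% events in both arms and a 3.5% margin, the one-sided 95% Agresti-Caffo limit first reaches 80% power at 131 evaluable patients per arm (80.8%). Then 131 / 0.95 = 137.9, that is 138 per arm and 276 in total.

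**Approximation.** Let φ = variance/mean = 1 + kμ. With n per arm, the difference between the two arm totals has variance 2nμφ, while the Poisson test uses about 2nμ. The test statistic therefore has variance φ, not 1:

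- actual type I error ≈ 2[1 − Φ(1.96/√φ)]
- a correct interval is √φ times as wide

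At φ = 1.5 this gives 11.0% and a factor of 1.22; at φ = 2, 16.6% and 1.41; at φ = 3, 25.8% and 1.73; at φ = 4, 32.7% and 2.0.

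**Simulation.** 138 per arm, no true difference, 40,000 trials per setting. Each cell shows the type I error of the exact test in %, with the coverage of the per-arm exact 95% Poisson interval in brackets.

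| Count (assumed mean) | k = 0 | k = 0.25 | k = 0.5 | k = 1 | k = 2 |
|---|---|---|---|---|---|
| Hospitalisations (0.1) | 3.0 (97.0) | 3.3 (96.7) | 3.4 (96.6) | 3.9 (96.1) | 4.8 (95.3) |
| Hospitalisations (0.2) | 3.6 (95.6) | 4.1 (95.1) | 4.7 (94.3) | 5.7 (93.3) | 7.8 (91.1) |
| ED visits (0.3) | 3.8 (95.7) | 4.5 (94.9) | 5.2 (94.3) | 6.8 (92.4) | 10.3 (89.2) |
| Outpatient visits (2) | 4.7 (95.3) | 10.5 (89.5) | 15.7 (83.9) | 24.7 (74.9) | 37.3 (62.6) |
| Outpatient visits (3) | 4.4 (95.2) | 13.2 (86.2) | 20.7 (78.7) | 31.8 (67.6) | 44.9 (54.2) |
| Outpatient visits (4) | 4.6 (95.4) | 15.9 (84.3) | 25.3 (75.4) | 37.7 (62.8) | 51.2 (49.4) |

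For outpatient visits at mean 2, φ is 1.5, 2 and 3 at k = 0.25, 0.5 and 1, and the simulated 10.5%, 15.7% and 24.7% agree with the approximation.

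**The alternative under the same conditions.** 131 per arm, 600 trials per setting, Monte Carlo standard error about 1 percentage point.

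| Mean, k | Exact Poisson (table above) | Negative binomial Wald | Robust-variance Poisson |
|---|---|---|---|
| 0.2, 1 | 5.7% | 4.2% | 4.2% |
| 3, 0.5 | 20.7% | 5.8% | 6.7% |
| 3, 1 | 31.8% | 6.0% | 6.2% |

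**The case against.** Four objections deserve weight.

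- **Overdispersion is not overlooked.** A reader might infer that the plan misses it. The article does not support that reading: it prespecifies a negative binomial model for the same counts, so a Poisson result driven by frequent attenders would have a corrective analysis beside it. This objection stands and lowers the priority. What remains is that the first-line result is the one open to error, and that no rule settles a disagreement.
- **Hospitalisations are hardly affected.** A reader might extend the point equally to every count named in the sentence. The table does not bear that out. At means of 0.1 to 0.2 the exact test is conservative or close to nominal unless dispersion is strong. This stands.
- **The size is assumed.** With k = 0 the test is below 5% throughout, and with k = 0.25 and mean 2 the error is 10.5%. Quoting only the higher dispersions would overstate what can be known from the article. The direction is secure for any overdispersion appreciable enough to outweigh the exact test's slight conservatism; the amount is not.
- **The consequence is limited.** The outcomes are ancillary. Resource utilisation also includes initial length of stay and time to return to work or usual activities, which are compared by Wilcoxon and log-rank tests and are untouched. A reader might take the point as casting doubt on the trial's main result. It does not, because the VTE comparison uses a separate method based on one binary outcome per patient.

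**Conclusion.** The point holds for outpatient visits and, to a small extent, for ED visits. The first-line analysis assumes variance equal to the mean for repeatable contacts, while the model that drops this assumption is placed lower. At an assumed mean of 2 outpatient visits the actual error of the nominal 5% test lies between about 10% and 37% for k from 0.25 to 2. For ED visits it is about 4% to 10%, and for hospitalisations about 3% to 8%, both ranges starting at k = 0.

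These figures rest on the assumed means, on negative binomial counts, and on reading the exact p value as the two-sided conditional Poisson test. ED visits are listed among the ancillary outcomes but not named in the sentence on count data, so treating them in the same way is also an assumption.

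This is a minor point. It affects how far a difference in visit counts can be believed. It does not affect the non-inferiority conclusion.

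**What to change.** Make the negative binomial rate ratio, with each patient's follow-up time as offset, the main comparison for hospitalisations, ED visits and outpatient visits. A rate ratio with robust variance would also serve. Take the per-arm 95% intervals from the same model. The crude rates need not be dropped; report them as description only, without the exact Poisson p value as the test of the hypothesis.

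The cost is small: the two analyses already planned change rank, and no new data or patients are needed. The intervals become wider, by about √φ. The replacement is approximate too, with a simulated error of 4.2% to 6.0% for the negative binomial test and 4.2% to 6.7% for the robust version.

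### At the plan's own event rates, the Fine-Gray models for VTE recurrence and bleeding will often meet an arm with no events, leaving no finite hazard ratio and a meaningless Wald p value (minor: a further secondary analysis)

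*Protocol article*

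**What the plan says.** The relevant text is in the protocol article, under Planned statistical analyses and Sample size calculation.

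- **Rank of the models.** "In a further secondary analysis, we will use model-based approaches for all outcomes".
- **Models named.** For VTE recurrence and clinically significant bleeding (and two other time-to-event outcomes), "we will use competing risk regression according to Fine and Gray", with death from other causes as the competing event. "For mortality, we will use Cox regression".
- **Planning rate for VTE.** "Assuming a baseline VTE recurrence proportion of 1.0% at 90 days in both treatment groups". The source cohort of 127 anticoagulated patients is cited as "showing a VTE recurrence risk of 0.8% at 90 days after diagnosis".
- **Planning rates for bleeding.** The margin is justified in part by "the substantially lower risk of clinically significant bleeding (<1% vs 7% within 3 months for patients receiving anticoagulants").
- **Size.** "we estimated that 276 patients (138 per group) would result in at least 80% power", with "a sampling ratio of 1:1 allowing 5% attrition".

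The same section anticipates sparse data for counts, where zero-inflation is to be considered. It says nothing comparable for the event outcomes. No mortality rate is given anywhere.

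**The concern.** A two-arm Fine-Gray or Cox model estimates a log hazard ratio from the events in both arms. If one arm has none, the partial likelihood keeps rising as the coefficient moves to minus or plus infinity. The software then either fails to converge or stops at an arbitrary large value. A Wald p value computed at that stopping point carries no information about the treatment effect.

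The plan expects one or two recurrences per arm, so this is an ordinary outcome of the trial and not a remote one. For bleeding it occurs exactly when surveillance does best, with no bleeds. At stake is the supporting relative-effect estimate for the primary outcome and for the main expected benefit. It could be unusable, or printed with a p value set by the software's variance estimator.

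**Working it through.** **1. The plan's sample size.** Inputs: 1.0% VTE in both groups, margin 3.5%, one-sided 5%, Agresti-Caffo upper limit, 5% attrition. Enumerating both binomials exactly gives power 0.808 at 131 per arm. Inflating for attrition, 131 / 0.95 = 137.9, so 138 per arm and 276 in total. The stated figure reproduces, so 131 (evaluable) and 138 (randomised) are the right arm sizes to use.

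**2. Expected VTE events.** 131 × 0.01 = 1.31 and 138 × 0.01 = 1.38 per arm.

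**3. Chance of an empty arm for VTE.** Let q = (1 − p)^n. Exactly one arm is empty with probability 2q(1 − q), and both with probability q².

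| p, both arms | n per arm | q | exactly one empty | both empty | at least one empty |
|---|---|---|---|---|---|
| 1.0% | 131 | 0.268 | 39.2% | 7.2% | 46.4% |
| 1.0% | 138 | 0.250 | 37.5% | 6.2% | 43.7% |
| 0.8% | 131 | 0.349 | 45.4% | 12.2% | 57.6% |
| 0.8% | 138 | 0.330 | 44.2% | 10.9% | 55.1% |

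The 0.8% rows apply the source cohort's rate to both arms. The planning value is 1.0%.

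**4. Chance of no bleeding under surveillance.** The stated rate is below 1%, so 1% gives a lower bound: 0.99^131 = 26.8% and 0.99^138 = 25.0%. At an assumed 0.5%, 0.995^131 = 51.9% and 0.995^138 = 50.1%. Under rivaroxaban at 7%, 131 × 0.07 = 9.2 to 138 × 0.07 = 9.7 bleeds are expected, and an empty arm has probability below 0.01%.

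**5. What a Fine-Gray fit returns with one empty arm.** Simulated data, 138 per arm, with one competing death in each arm. Events are surveillance v rivaroxaban.

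| Events | Fit | Log HR | SE | Wald p |
|---|---|---|---|---|
| 0 v 2 | R cmprsk `crr`, default iterations | did not converge | – | – |
| 0 v 2 | `crr`, 100 iterations, sandwich SE | −15.2 | 0.71 | 0 |
| 0 v 2 | weighted Cox, model-based SE | −20.2 | 17,238 | 0.999 |
| 0 v 2 | weighted Cox, robust SE | −20.2 | 0.71 | about 10⁻¹⁷⁸ |
| 0 v 10 | `crr`, 100 iterations, sandwich SE | −15.2 | 0.33 | 0 |
| 0 v 10 | weighted Cox, model-based SE | −20.2 | 7,711 | 0.998 |

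Fisher's exact p for 0 v 2 is 0.50. So one data set yields p = 0.999 or p = 0 according to the variance estimator, and neither reflects the evidence.

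**6. Does penalisation help?** Firth-penalised Cox fits with profile-likelihood limits, 131 per arm, no competing deaths:

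- 0 v 9: HR 0.051 (95% CI 0.0004 to 0.40), p = 0.0014; Fisher p = 0.003.
- 0 v 2: HR 0.20 (95% CI 0.001 to 2.4), p = 0.23; Fisher p = 0.50.

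Both are finite and lead to the same conclusion as the exact test. With no events in either arm there are no terms in the partial likelihood, and penalisation cannot supply an estimate.

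**The case against.** **Nothing decisive rests on these models.** This stands. Non-inferiority is judged on the Agresti-Caffo limit, bleeding and mortality on Agresti-Caffo risk differences with an exact test, and competing death is also handled by cumulative incidence differences. A reader might infer that the trial's conclusion is at risk, but the documents do not support that.

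**Estimation detail belongs in the analysis plan.** This stands in part. The article does not say ordinary likelihood or Wald inference; those are the usual defaults of the named methods. The article states that a statistical analysis plan exists, and it may hold a fallback, so the lack of one here is no finding. What remains is that the named models, fitted in the standard way, often have no finite estimate at the article's own rates.

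**The p value is not always near 1.** Correct. A reader might infer that a strong bleeding result such as 0 v 9 would necessarily be printed with p near 1, against the exact test. That holds only for a Wald test with the model-based standard error. With the sandwich error p falls to about 0, and in a plain Cox fit the score and likelihood-ratio tests stay finite (0 v 10: p = 0.001 and 0.0002).

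**Firth is one choice among several.** Fair. The check in step 6 used Cox fits, while Fine-Gray with censoring weights is a weighted pseudo-likelihood, for which penalised profile limits are not automatically exact. The concern is eased by the expected near-complete 90-day follow-up: with little early censoring, the subdistribution risk set needs almost no weighting. With about 2.6 expected recurrences in total, any VTE hazard ratio will be very imprecise.

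**Conclusion.** The concern holds in a limited form and is minor. At the planning rates, exactly one arm has no VTE in about 37–39% of trials and neither has any in about 6–7%. The surveillance arm has no bleeding in at least about 25–27%. With one empty arm, the standard fit of the planned model has no finite hazard ratio, and its Wald p value is an artefact of the variance estimator. With both arms empty there is nothing to estimate, so it would be wrong to describe all 44–46% of VTE cases as a zero or infinite hazard ratio.

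These probabilities assume independent binomial counts at the stated rates. The 50–52% figure for bleeding rests on an assumed 0.5%. No size can be given for mortality from the document: if the rate were 1% in each arm, the 1.0% rows in step 3 would apply, but that rate is an assumption.

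**What to change.** Under Planned statistical analyses, where the Fine-Gray and Cox models are named, add wording to this effect:

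- Fit the models for VTE recurrence, clinically significant bleeding and mortality with Firth's penalised likelihood. For Fine-Gray, fit it as a Cox model on the subdistribution risk set.
- Take confidence intervals and p values from the penalised profile likelihood and not from Wald statistics.
- If neither arm has an event, report no hazard ratio and rely on the risk difference.

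If the statistical analysis plan already has an equivalent rule, a cross-reference is enough. The rule should be fixed before unblinding, so that the rescue method is not chosen after the counts are known.

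The cost is a few lines of text and a modest amount of programming. The penalised estimate shrinks slightly toward 1, and intervals will be very wide with few events. If random site effects are added, as the article allows, combining them with the penalty needs separate thought. No change is needed to the primary test, the exact secondary tests or the sample size.
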